#### Regression models

We will perform multi-level logistic regressions with the cumulative incidence of depression at 18 months as the dependent variable. To test the hierarchical data structure we will use the likelihood-ratio test of the null model with health center as a random factor versus usual logistic regression. Then we will check the likelihood-ratio test of the null model with health center and FP as random factors versus the null model with only health center. We will also calculate the intraclass correlation coefficients for health center and FP.

We will include in the models the group variable (control and intervention) and will adjust for the probability of the onset of major depression at 12 months measured at baseline [34]. Where appropriate we will adjust for unbalanced variables at baseline not included in the equation to predict the onset of major depression [34]. We also will retain in the model the variable city because of an a priori assumption of clustering effect within city, although it has few categories (n = 7) that could be considered as random factors [83]. From the final model we will obtain the adjusted odds ratio (OR) of the group variable and the adjusted number needed to treat, $\mathrm{NNT}=\frac{1}{\mathrm{lo}\left(1-\mathrm{OR}\right)}$ [Io = cumulative incidence in control group], to prevent a case of major depression.

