### Randomized allocation

The randomization and allocation to the arms will be carried out according to the health center; that is, all FPs and patients from one health center will be included in the same arm. If the same health center has FPs in both the control and the intervention groups, the likelihood of the FPs in the control group becoming contaminated by the intervention group is high, since Spanish health centers generally work as a team. We aim to evaluate a new intervention for primary prevention of major depression, which in principle will be delivered at patient level by the FP; however, due to the nature of the intervention some components could be delivered at community level, so the contamination between patients in the control and intervention groups in the same health center is likely. Therefore we have decided on cluster randomization to avoid this possibility in patients and FPs.

The randomization of the 70 health centers to allocate them to the control or intervention groups will be done stratifying by city. Thus, we will have 35 health centers assigned to the control group and 35 to the intervention group, 5 and 5 respectively for each one of the seven cities participating in our study. The randomization will be undertaken centrally, from the coordinating center in Malaga, by an independent person outside the research group using closed and opaque envelopes.

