### Sample size

The sample size was calculated assuming that the cumulative incidence of depression in the control group will be 12% [34] while the incidence in the intervention group will be 5 points below that 12%. The Type I error of the chosen contrast was 5% and the power 80%. The sample size obtained assuming a simple random sample would be 430 people in each group. As we will undertake a cluster randomization (by health center), and decided to have 35 health centers in the control group and 35 in the intervention group (48 patients in each health center), we obtained an effect design of 3.82, with the assumption that the intraclass correlation coefficient of the health center is 0.06 [34]. Thus we need a sample size of 1643 patients in each trial arm, making a global sample of 3286 patients, 140 family doctors and 70 health centers. These calculations assume that the distribution of 2 FPs per health center and 24 patients per FP will be very homogeneous (coefficients of variation of cluster sizes <0.15). We also expect to increase the sample of patients recruited by FPs from 24 to 26–27, since about 10% of potential patients will have a diagnosis of major depression on CIDI at baseline and will need to be excluded.

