#### Cost effectiveness and cost-utility analysis

As in the effectiveness analyses, we will take two approaches to the cost-effectiveness and cost-utility analyses: 1) a complete case analysis with covariate adjustment and 2) an analysis after multiple imputations with covariate adjustment. For the first strategy we will apply the inverse probability weighting to the final model. We will calculate incremental cost-effectiveness ratios (ICER), which are calculated as incremental cost (mean cost for intervention group minus mean cost for control group) divided by incremental effectiveness (mean effect for intervention group minus mean effect for control group) [93]. Incremental cost-utility ratios (ICUR) will be calculated in the same way. The only difference is that the effect will be the difference in QALYs. The incremental costs and incremental health effects will be modeled by generalized linear models (GLM). The modified Parks test will be used in order to select the appropriate family. In order to identify the correct link function we will compare model performance of all permutations of candidate link and variance function using different diagnostic tests such as the Pregibon Link test, the Hosmer-Lemoshow test and the Copas test [93]. We will check the intraclass correlation coefficients and the likelihood-ratio tests with health center, FP and both as we said before. If the clustering effect is relevant, we will use robust standard errors for the cluster indicated.

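### The health-centre effect is put to a significance test without a statement that it stays in the effectiveness model, although centres are the unit randomised; the economic models make allowance for clustering conditional

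*Protocol article*

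**What the plan says.** All references are to the protocol article.

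- **Randomized allocation:** "The randomization and allocation to the arms will be carried out according to the health center", and "we will have 35 health centers assigned to the control group and 35 to the intervention group".
- **Sample size:** the simple-random-sample size is multiplied by a design effect of 3.82, based on 48 patients per centre and a centre ICC of 0.06.
- **Regression models:** the section opens by announcing multilevel logistic regression for the 18-month outcome. It then describes a "likelihood-ratio test of the null model with health center as a random factor versus usual logistic regression", followed by a second test of adding the family physician (FP) to the centre model. City is kept because clustering within city is assumed in advance. The odds ratio and number needed to treat come from the final model. Nothing states what follows a non-significant first test, and nothing says that centre is kept regardless.
- **Cost effectiveness and cost-utility analysis:** the authors will look at the ICCs and the "likelihood-ratio tests with health center, FP and both as we said before". Robust standard errors for the level so indicated are used only if the clustering is found relevant.

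**The concern.** When whole centres are allocated, the treatment contrast is a comparison between centres, and its standard error must contain the between-centre variance. A non-significant variance test does not show that this variance is zero. With about 47 patients per centre, an ICC too small for the test to detect reliably still widens the true sampling error.

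Three features of the Regression models section make the test look like a selection step: its comparator is ordinary logistic regression, it is the first of two nested tests leading to a final model, and city alone is exempted from testing. If centre were dropped on this basis, the confidence interval and p-value of the primary outcome would ignore the unit randomised. For costs and QALYs the dependence on the test is explicit. The article gives no ICC for those outcomes, so the 0.06 assumption offers no reassurance there.

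**Working it through.** **1. The plan's own clustering figure.** Design effect = 1 + (m − 1) × ICC = 1 + 47 × 0.06 = 3.82, and 430 × 3.82 = 1642.6, i.e. 1643 per arm. Both figures reproduce. The planned sample averages 3286 / 70 = 46.9 patients per centre.

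**2. Understatement if centre is ignored.** The ordinary standard error is too small by a factor of √(1 + 47 × ICC):
- ICC 0.005: √1.235 = 1.11
- ICC 0.01: √1.47 = 1.21
- ICC 0.06: √3.82 = 1.95

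**3. How often the test would drop centre, and what follows.** Inputs from the article: 70 centres (35 per arm), 12% incidence, ICC 0.06. Assumptions not in the article: ICCs below 0.06, 38 patients per centre as an attrition scenario, and a 5% cut-off from the 50:50 mixture chi-square distribution (2.71). There is no true treatment effect. The rule examined is to use ordinary logistic regression if the centre test is non-significant and a clustered analysis otherwise.

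Simulation A: beta-binomial clustering, 47 per centre, 2000 trials per ICC, with a cluster-level t-test as the clustered analysis. The last four columns are false-positive rates.

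| ICC | Centre dropped | Ordinary model always | Ordinary model, dropped trials only | Test-then-choose, all trials | Clustered analysis always |
|---|---|---|---|---|---|
| 0.0025 | 85% | 6.25% | 5.8% | 5.55% | 4.95% |
| 0.005 | 69% | 7.45% | 6.8% | 5.95% | 5.15% |
| 0.01 | 32% | 11.25% | 8.2% | 7.0% | 6.05% |
| 0.015 | 9% | 13.35% | 7.9% | 5.3% | 5.15% |
| 0.02 | 2% | 16.75% | 4.9% (41 trials) | 5.3% | 5.3% |
| 0.06 | 0 of 2000 | 31.1% | none | 4.55% | 4.55% |

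Simulation error is about 0.5 point in the columns based on all trials. It is larger among dropped trials: at ICC 0.015 these number 0.0885 × 2000 = 177, giving √(0.079 × 0.921 / 177) = 2.0 points.

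Simulation B: logit-normal centre effects, 5000 trials per setting, with mixed logistic regression as the clustered analysis. Test-then-choose against centre always kept:
- ICC 0.005: 5.9% against 5.1% (47 per centre); 5.8% against 5.1% (38 per centre).
- ICC 0.01: 6.1% against 5.7%; 6.0% against 5.3%. Centre is dropped in 30% and 45% of trials, with error in those trials of 7.6% and 6.6%.
- ICC 0.015: 5.5% against 5.4%; 5.8% against 5.3%. Centre is dropped in 10 to 20% of trials, with error in those of about 8%.
- ICC 0.06 (1500 trials): centre is never dropped.

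**4. Size of the overall excess.** The largest difference is 7.0 − 6.05 = 0.95 point in simulation A (ICC 0.01) and 5.9 − 5.1 = 0.8 point in simulation B (ICC 0.005). The two simulations agree although their clustering models and clustered tests differ.

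**The case against.** A reader might infer that the plan commits the primary analysis to ordinary logistic regression after a non-significant test. The article does not say so. The Regression models section and the Abstract both announce multilevel logistic regression without condition. The Inverse probability weighting section runs the weighted final model in GLLAMM, a multilevel program. That section also makes a multilevel form conditional for the attrition model, and no such qualifier is attached to the outcome model. In the cost section, the reference back points to the tests and ICCs; it does not carry the conditional rule over to the effectiveness model. All of this stands, so for the primary outcome the point is an opening left in the text and not a stated rule.

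A reader might also take the 31.1% error at ICC 0.06 as the risk to this trial. It is not: at that ICC the test kept centre in every simulated trial, so the ordinary model would not be used.

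The simulations also leave out city and baseline risk. The null model has no covariates, so differences between cities and in case mix add to the variance tested and make dropping centre less likely. The later adjustment can shrink the residual centre variance that an ordinary model would ignore. Both tend to make the real harm smaller than simulated.

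Finally, what follows a test could be left to an analysis plan that is not shown. That answers part of the point for the primary outcome. It does not answer the economic analysis, where the article itself writes the conditional rule.

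**Conclusion.** The point holds as a low-severity improvement. The effectiveness section leaves open whether the unit randomised stays in the primary model, and the economic section makes allowance for clustering depend on a judgement of relevance. Any positive centre ICC makes standard errors too small if centre is dropped.

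For the primary outcome the consequence is nil at the planned ICC of 0.06. At assumed ICCs of about 0.005 to 0.015, the false-positive rate is about 7 to 8% in trials that drop centre, with an overall excess under about 1 point. These figures rest on the assumed ICCs, the mixture cut-off, the omission of covariates and the supposition that a non-significant test would lead to ordinary logistic regression. For costs and QALYs the size cannot be given, because the article states no ICC for them.

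**What to change.** In Regression models, state that the health-centre random effect is kept in every effectiveness model whatever the likelihood-ratio test shows. Report that test and the ICCs as description only, and let testing decide only whether the FP level is added.

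In Cost effectiveness and cost-utility analysis, replace the conditional rule with standard errors clustered by health centre in all cost and QALY models.

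The cost is about two sentences. No extra patients or data are needed and the sample size does not change. The interval may be slightly wider when clustering is near zero. In simulation A, the clustered analysis used throughout gave false-positive rates close to 5%, allowing for simulation error.

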### The ‘predictD’ algorithm

In recent years, our research group has developed and validated a risk algorithm (“the predictD algorithm”) to predict the onset of episodes of major depression in primary care attendees, in Europe [33] and Spain [34]. The Spanish algorithm obtained good calibration and discriminative validation [C-index = 0.82 (0.79-0.84)]. From 39 known risk factors of depression, 12 were included in the Spanish prediction model: six were patient characteristics or past events (sex, age, sex*age interaction, education, childhood physical abuse, and lifetime depression) and six were current status (SF-12 physical score, SF-12 mental score, dissatisfaction with unpaid work, number of serious problems in very close persons, dissatisfaction with living together at home, and taking medication for stress, anxiety or depression). The calculator of the likelihood of becoming depressed at 12 months is accessible at http://www.rediapp.org/predict.php. The "predictD algorithm" provides, in addition to the quantification of the overall risk of depression, knowledge of those risk factors influencing a given patient and that could guide a possible preventive intervention. This could allow us, as in cardiovascular disease, to develop interventions tailored in both intensity (level of risk) and specificity (profile of risk). This type of primary prevention might be called “*personalized prevention*” [35,36].

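### The NNT formula treats the adjusted odds ratio as a risk ratio, so the reported NNT will be too small whenever the intervention is protective

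*Protocol article*

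**What the plan says.** Under Regression models, the protocol article plans multilevel logistic regression of depression over 18 months. Health center, and possibly family physician, enter as random factors, subject to likelihood-ratio tests. The model contains trial arm, the baseline predictD probability, city and, where appropriate, variables unbalanced at baseline. The section continues: "From the final model we will obtain the adjusted odds ratio (OR) of the group variable and the adjusted number needed to treat". The printed formula is NNT = 1/[Io(1 − OR)], with the definition "Io = cumulative incidence in control group". No step converts the odds ratio to a risk.

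Two other sections supply the figures needed to judge the effect. Sample size assumes that "the cumulative incidence of depression in the control group will be 12" per cent and that "the incidence in the intervention group will be 5 points below that 12" per cent, with a health-center intraclass correlation of 0.06. The Background section on the predictD algorithm reports its discrimination as "C-index = 0.82 (0.79-0.84").

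**The concern.** An NNT is the reciprocal of a risk difference. The product Io(1 − X) equals the risk difference Io − I1 only when X is the risk ratio I1/Io. The plan puts an odds ratio there, and two errors follow, both in the same direction.

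- **Odds ratio used as a risk ratio.** For a protective effect the odds ratio lies further below 1 than the risk ratio.
- **Conditional odds ratio combined with a marginal risk.** The odds ratio is non-collapsible. Conditioning on a strong predictor, and on a center effect if retained, moves it further from 1 than the odds ratio that compares the two arms' overall risks. Io, however, is an overall risk.

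The NNT is the only absolute effect measure named in the effectiveness analysis. A health service reading it would take the program to need fewer patients per case prevented than the data show. It would also disagree with the economic evaluation, which takes the difference in cumulative incidence as its health effect.

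**Working it through.** **Inputs.** Io = 0.12, I1 = 0.07 and ICC = 0.06 (Sample size); C-index 0.82, interval 0.79 to 0.84 (Background). The article states no NNT, so there is none to reproduce. The clustering inputs do agree with the stated design: 1 + (48 − 1) × 0.06 = 3.82, and 430 × 3.82 = 1642.6, which is the stated 1643 per arm.

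**Target.** Risk difference = 0.12 − 0.07 = 0.05, so NNT = 1/0.05 = 20. Risk ratio = 0.07/0.12 = 0.583.

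**Step 1: crude odds ratio.** OR = (0.07/0.93)/(0.12/0.88) = 0.552. The formula gives 1/[0.12 × (1 − 0.552)] = 18.6, which is 7% too small. In general 1 − OR = (Io − I1)/[Io(1 − I1)], so the formula returns the true NNT multiplied by (1 − I1). With a crude odds ratio the proportional shortfall therefore equals the intervention-arm risk, here 7%.

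**Step 2: conditional odds ratio.** Assume a logistic model whose linear predictor varies normally between patients (score) and between centers (random effect). Choose the score SD to give the stated C-index at 12% risk; C = 0.82 needs an SD of 1.44. The article does not give the scale of the ICC, so take both readings:

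- latent scale: center SD = √[(0.06/0.94) × π²/3] = 0.458
- proportion scale: center SD = 0.753, found numerically

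Then solve for the two intercepts that give overall risks of 12% and 7%. Their difference is the log conditional odds ratio. Where two values are shown, the first uses the latent and the second the proportion scale.

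| Conditioning | OR | NNT from formula | Shortfall against 20 |
|---|---|---|---|
| None (crude) | 0.552 | 18.6 | 7% |
| Center only | 0.546; 0.535 | 18.4; 17.9 | 8%; 10% |
| Score, C = 0.82, no center effect | 0.489 | 16.3 | 18.5% |
| Score, C = 0.75, plus center | 0.514; 0.503 | 17.2; 16.8 | 14%; 16% |
| Score, C = 0.79, plus center | 0.499; 0.488 | 16.6; 16.3 | 17%; 19% |
| Score, C = 0.82, plus center | 0.483; 0.473 | 16.1; 15.8 | 19.5%; 21% |
| Score, C = 0.84, plus center | 0.469; 0.460 | 15.7; 15.4 | 21.5%; 23% |

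At C = 0.82 with the latent-scale ICC, the formula implies a reduction of 0.12 × (1 − 0.483) = 0.062, or 6.2 points where the truth is 5.

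**Step 3: check by fitting.** Models fitted to 2,000,000 simulated records at C = 0.82, with the score entered as a logit or as a probability, and with or without a center effect, gave NNTs of 15.9 to 16.4 from the formula. Averaging predicted risks under each arm from the fits with a latent-scale center effect gave about 20.1.

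**Step 4: would better algebra be enough?** Apply OR = 0.483 to the control odds: 0.1364 × 0.483 = 0.0658, a risk of 0.0658/1.0658 = 0.0617. The difference is 0.0583 and the NNT 17.2. Converting the odds ratio correctly removes only the first error.

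**The case against.** The formula itself has no real defence: it is printed in full with its term defined, so it cannot be put down to detail left to another document. The case on the other side concerns size and importance, and much of it stands.

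- **Size.** A reader might infer that the NNT is about 20% too small at the trial's own design values. The documents do not support that. The Sample size figures alone give 7% to 10%. Going further needs the C-index from the Background, which refers to 12-month prediction, to hold for the 18-month outcome in this sample. It also needs a roughly normal linear predictor.
- **Center effect.** The random effect is tested first and may be dropped. This matters little: at C = 0.82 the NNT is 16.3 without it and 15.8 to 16.1 with it.
- **Importance.** A reader might take the NNT for the trial's headline measure. Nothing in the article says so. It is absent from the objectives and from the primary and secondary outcomes, and appears as one derived quantity in the regression section.
- **Reach.** A reader might also suppose that the cost-effectiveness results inherit the error. They do not: the economic evaluation works from the incidence difference and differences in means.
- **Precision.** With 430 effective patients per arm, the standard error of the difference is √[(0.12 × 0.88 + 0.07 × 0.93)/430] = 0.020. The 95% interval is about 1.1 to 8.9 points, an NNT of about 11 to 91. A shift from 20 to 16 lies well inside it.

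The last point limits the damage but does not excuse the formula. Sampling error has no preferred direction, whereas this error favors the intervention whenever it works.

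**Conclusion.** The concern holds for the reported NNT and should be fixed. The direction is certain for any protective effect. At the planned 12% and 7%, the shortfall is 7% from using an odds ratio as a risk ratio, and 8% to 10% if only a center effect at ICC 0.06 is added. It is about 17% to 23%, an NNT of about 16 against a true 20, if the predictD score performs at 18 months as reported (C-index 0.79 to 0.84), its linear predictor is roughly normal and the center effect is present. A weaker score, at C = 0.75, gives about 14% to 16%. The larger figures are therefore conditional on the score's performance; the 7% is not. The primary test, the odds ratio, the sample size and the economic evaluation are unaffected.

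**What to change.** Replace the formula with marginal standardisation from the final model. For each patient, predict the risk of depression under control and under intervention, integrating over the center effect if it is retained. Average each set of predictions over the sample. Report the adjusted risk difference beside the odds ratio, and NNT as the reciprocal of that difference. Give a confidence interval that respects clustering and imputation, for example by the delta method or by resampling whole centers, combined over the imputed datasets.

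The cost is modest: a changed sentence in the analysis section and some extra analysis work, mainly for integrating over centers and for the interval. It needs no new data and leaves the planned model and primary test as they are. If the intervention works, the reported NNT will be less favorable than under the current formula.

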#### Inverse probability weighting

For each patient the probability of remaining in the follow-up at 18 months will be obtained through a logistic regression model (multilevel if appropriate) with the variable ‘remaining in the follow-up’ (yes/no) as dependent variable and a set of predictor variables measured at baseline. For the effectiveness analyses with complete cases we will apply the inverse probability weighting to the final model to adjust for a possible attrition bias due to participants lost during the follow-up [84,85], implemented through the ‘GLLAMM’ program [86].

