### Variables

#### Main outcome

Our primary outcome will be the cumulative incidence of major depression during 18 months of follow-up. We will use the section of depression of the CIDI [54,55], developed and validated by the WHO [56]. The CIDI is a fully structured diagnostic interview that provides current diagnoses according to DSM-IV categories. We will use it to estimate the onset of major depression in each prior 6-month period (0–6, 6–12, and 12–18 months). Interviewing in this way, at baseline, 6, 12 and 18 months, we will obtain the most accurate picture of the cumulative incidence of major depression.

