• Probability of the onset of major depression at 12 months, obtained from the equation “predictD-Spain”, which has been previously validated [34] and is derived from a combination of some of the above variables.

We will assess all these variables and questionnaires at baseline, 6, 12 and 18 months. The test–retest reliability of questions used in the predictD studies has been reported previously [62,71].

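### The complete-case weights model retention at 18 months from baseline data alone, so they cannot correct dropout that follows depression already recorded at 6 or 12 months

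*Protocol article*

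**What the plan says.** The Inverse probability weighting section states that "the probability of remaining in the follow-up at 18 months will be obtained through a logistic regression model", with remaining in follow-up (yes/no) "as dependent variable and a set of predictor variables measured at baseline". On use of the weights it says: "For the effectiveness analyses with complete cases we will apply the inverse probability weighting to the final model". The section on cost-effectiveness and cost-utility analysis carries them over to its complete-case strategy: "For the first strategy we will apply the inverse probability weighting to the final model".

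The outcome accumulates over visits. Under Main outcome: "Our primary outcome will be the cumulative incidence of major depression during 18 months of follow-up", with the CIDI used "to estimate the onset of major depression in each prior 6-month period". The list of patient variables, which includes anxiety and the predicted risk of depression, ends: "We will assess all these variables and questionnaires at baseline, 6, 12 and 18 months". The SF-12 is also repeated at these visits (Secondary outcomes).

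The Statistical analysis section lists two effectiveness analyses: one with covariate adjustment, and an intention-to-treat analysis by multiple imputation. The Multiple imputations section allows any covariate of interest that predicts missingness and does not restrict these to baseline. The article does not define a complete case.

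**The concern.** Two features of the weighting do not fit this outcome.

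- **The modelled event.** A patient who is CIDI-positive at 6 or 12 months has a known outcome whatever happens next. If that patient then leaves, the retention indicator is 'no'. If complete cases are those still present at 18 months, a recorded event is dropped. If such patients are kept instead, the weight for reaching 18 months is the wrong weight for them, because their outcome was determined earlier.
- **The predictors.** Baseline-only weights assume that, given baseline, leaving is unrelated to what was recorded during follow-up. Where depressed patients leave more often, the weights cannot see it, although the 6- and 12-month data that would show it are collected.

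At stake are the incidences in this analysis, the number needed to treat (which uses the control incidence) and, in the economic complete-case analysis, the incidence difference used as the effect measure. The odds ratio is also at stake if the excess dropout differs between arms.

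**Working it through.** **Inputs from the protocol article (Sample size).** Control incidence 12%; intervention 12 − 5 = 7%; 1643 patients per arm. The last figure follows from the article's own numbers: 430 × [1 + (48 − 1) × 0.06] = 430 × 3.82 = 1642.6.

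**Assumptions (the article gives no dropout figures).** Constant onset hazard over three intervals. Dropout per interval is d = 7% without recorded onset and q after it. Dropout is unrelated to baseline, so baseline-only weights are constant within an arm and leave the incidence unchanged. Complete cases are patients present at 18 months.

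**Step 1, control arm, q = 14%.** Hazard h = 1 − 0.88^(1/3) = 0.0417. New recorded onsets at each visit = patients without onset × 0.93 × h:

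| Visit | New onsets | Without onset, in follow-up | Recorded cases lost since last visit |
|---|---|---|---|
| 6 months | 63.7 | 1464.2 | 0 |
| 12 months | 56.8 | 1304.9 | 63.7 × 0.14 = 8.9 |
| 18 months | 50.6 | 1163.0 | 111.6 × 0.14 = 15.6 |

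Here 111.6 = 63.7 − 8.9 + 56.8. Recorded onsets total 171.2, of which 24.6 are lost and 146.6 remain. Complete-case incidence = 146.6 / (146.6 + 1163.0) = 11.2%.

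**Step 2, intervention arm, q = 14%.** h = 1 − 0.93^(1/3) = 0.0239. Recorded onsets 99.8, lost 14.2, remaining 85.6. Incidence = 85.6 / (85.6 + 1229.0) = 6.5%. Over both arms about 39 of 271 recorded events (14%) are lost.

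**Step 3, effect measures.** OR = odds(intervention) / odds(control). NNT uses the article's formula as written, 1 / [Io(1 − OR)].

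| Dropout after onset, control / intervention | Incidences | OR | NNT |
|---|---|---|---|
| No bias | 12.0% / 7.0% | 0.5520 | 18.6 |
| 7% / 7% | 12.0% / 7.0% | 0.5520 | 18.6 |
| 14% / 14% | 11.2% / 6.5% | 0.5525 | 20.0 |
| 21% / 21% | 10.4% / 6.0% | 0.5531 | 21.5 |
| 14% / 28% | 11.2% / 5.6% | 0.470 | – |
| 28% / 14% | 9.7% / 6.5% | 0.650 | – |

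In the 7% / 7% row about 12.6 recorded control events are still lost, yet the incidence stays at 12.0%. So about half of the 24.6 lost at 14% is lost precision and not bias. With no true effect (12% in both arms), 14% / 28% gives 11.2% against 9.7%, and 28% / 14% gives the mirror image.

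**Step 4, do updated weights repair it?** A simulation of 1.5 million patients without clustering, with dropout related to a baseline risk score and to recorded onset, compared baseline-only weights with weights built from the true retention probabilities including recorded onset:

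| Dropout per interval after onset, control / intervention | Full-data OR | Baseline-only weights | Updated weights |
|---|---|---|---|
| 15% / 30% | 0.552 | 0.464 | 0.549 |
| 30% / 15% | 0.545 | 0.650 | 0.549 |
| 20% / 20% | 0.548 | 0.545 | 0.546 |

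In the last row incidences of 10.9% / 6.5% fall to 9.6% / 5.7% with baseline-only weights and return to 10.9% / 6.5% with updated weights.

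**Step 5, is counting early events enough?** No. Without suitable weights the control incidence becomes 171.2 / (171.2 + 1163.0) = 12.8%, because patients who leave without onset are still lost. If each patient is weighted up to the visit that determines the outcome, the factors 0.93 cancel. Cases then sum to 1 − (1 − h)³ = 12% and non-cases to (1 − h)³ = 88%.

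**The case against.** **The discarding is inferred.** A reader might take the article to say that early onsets are thrown away. It does not: it defines the dependent variable of the weight model, and complete case is left undefined. This stands. But either reading needs repair, because keeping those patients leaves them with the wrong weight.

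**Another analysis can deal with the problem.** The abstract ties the intention-to-treat effectiveness analysis to multiple imputation, which can keep recorded onsets and use interim data. This stands, so it would be wrong to infer that the trial's main result is in danger. Still, Strengths and limitations relies on the weighting to adjust the complete-case analyses for attrition bias, and it cannot do so for dropout that follows recorded depression.

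**The planned effect measure hardly moves.** With equal dropout after onset, the odds ratio is essentially unbiased. This stands; only incidences, their difference and the NNT shift, and only if depressed patients leave more often.

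**Bias between arms rests on assumed inputs.** Under Side effects of the intervention, patients may refuse the risk information at each evaluation point and are then excluded, and control patients never receive that information. A reader might infer a bias in favour of the intervention. The article does not link this exit to depression, so neither the existence nor the direction of such a bias follows.

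**Economic data.** A patient who leaves after an early onset still has no 18-month costs or QALYs. This stands: counting the event does not complete that case.

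**Conclusion.** The point holds for the weighted complete-case analyses, effectiveness and economic. The weight model is fixed in a form that ignores the 6- and 12-month data and does not match when the outcome becomes known.

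Its size depends on dropout rates that the article does not give. With 7% per interval and 14% to 21% after onset, the control incidence falls from 12% to between 11.2% and 10.4%, the intervention incidence from 7% to between 6.5% and 6.0%, and the NNT rises from 18.6 to between 20.0 and 21.5. The odds ratio stays near 0.55 unless the excess dropout differs by arm. A two-fold difference moves it to about 0.47 or 0.65, depending on which arm loses more depressed patients.

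This is worth correcting in a complementary analysis. It does not show that the intention-to-treat inference is unsound.

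**What to change.** Keep the multilevel logistic model and its 18-month odds ratio. A discrete-time or complementary log-log model would change the effect measure without need. For the complete-case effectiveness analysis, state that:

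1. Any CIDI onset at 6 or 12 months counts as an event, whatever the later follow-up.
2. Each patient is weighted by the inverse of the product of interval-specific retention probabilities (0–6, 6–12, 12–18 months) up to the visit at which the outcome is determined: first onset, or 18 months for those without onset.
3. The retention models include arm and predictors updated at each visit.

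Items 1 and 2 must go together, since counting early events alone overstates incidence.

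For the economic complete-case analysis, use the updated weights for retention to 18 months, with recorded onset among the predictors.

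The cost is a change of wording, modest programming and somewhat more variable weights. All the data are already collected. The updated weights still assume that leaving is unrelated to an onset not yet recorded at the last visit attended, and the report should say so.
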